**Figure 1 F1:**
[figure not shown]
Study participant’s flow chart.

### Measures

The primary outcome measures are the incidence of dental decay in primary teeth and the prevalence of obesity. Children will be examined at the dental therapy clinics of the DHS of Western Australia for the incidence of dental decay by two blinded, calibrated examiners at 24 and 36 months of age, using the criteria specified by Workshop on Reporting Early Childhood Caries [51] and at 60 months using the criteria of the WHO [52].

Examiner training will involve examination of early childhood decay under the guidance of a specialist paediatric dentist. Further examiner calibration will be undertaken by examination of 10 children consenting to participate in an oral screening program of DHS. During field examinations, approximately 5% of study participants will be re-examined to test for intra- and inter-examiner reliability. Child height/length and weight will be measured and Body Mass Index calculated (BMI; weight/height^2^) and BMI z score determined at 24 and 36 months, using the age-specific WHO growth standards [53]. Number needed to treat as an effect measure of the program will be estimated [54]. Examiner training will be repeated for each cycle of the clinical examinations to maintain reliability over the course of the study.

Secondary outcome measures will be changes in knowledge, attitude, behaviour and self-efficacy of parents towards the oral health of their child and differences in nutritional and dietary patterns between groups. Long-term outcomes will be the incidence of dental decay and referral for care under general anaesthesia among the groups when the child is 5 years of age.

### Data protection

The research will adhere to guidelines within the Australian Code for the Responsible Conduct of Research [55]. All collected data will be transcribed into electronic format and stored on a password-protected computer accessible only by the researchers. A separate electronic file will be created, excluding identification data for data analysis.

### Data analysis

Oral health outcomes will be defined by counts of decayed, missing and filled teeth/surfaces and include non-cavitated lesions. Predictor variables will be on the basis of group allocation to intervention or control group and the posited psychosocial mediating variables will be defined using the approach adopted by Finlayson et al. [39].

Appropriate parametric and non-parametric statistics will be used to test the aims of the study. Differences in outcomes between the groups will be tested on an intention to treat and per protocol basis. Univariate analyses using t-tests for continuous variables (*oral health knowledge, behaviour, attitudes, self-efficacy and parental stress of parents/caregivers*), and Chi square analyses for categorical variables will be undertaken to examine the baseline factors and their association with group assignment. Univariate analyses will also be used to examine the association between the primary outcomes of dental decay incidence and prevalence, and early childhood obesity prevalence, with group allocation.

Multivariate analysis will be used to control for potential confounding factors to examine the effects of treatment strategies, and will use linear regression for continuous outcome variables and test for mediator effects using the approach outlined by MacKinnon and Luecken (2011) [56], logistic regression for binary outcomes (dental decay prevalence, obesity prevalence) and Poisson regression to estimate rates of disease occurrence. Site-specific measures of caries incidence within an individual will use GEE analysis to control for correlation within an individual. Effect size will be estimated through calculation of incidence density ratios for dental decay and prevalence ratios for obesity. Effect measures will also be presented through calculation of number needed to treat and its associated 95% confidence interval. The statistically significant level will be at α = 0.05.

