**Methods:**

The study will be a randomised controlled study with parents and their new-born child/ren who are seen at 6–12 weeks of age by a child/community health nurse. Consenting parents will complete a questionnaire on oral health knowledge, behaviours, self-efficacy, oral health fatalism, parenting stress, prenatal and peri-natal health and socio-demographic factors at study commencement and at 12 and 36 months. Each child–parent pair will be allocated to an intervention or a standard care group, using a computer-generated random blocks. The standard group will be managed through the standard early oral health screening program; “lift the lip”. The intervention group will be provided with tailored oral health counselling by oral health consultants trained in MI and AG.

Participating children will be examined at 24, and 36 months for the occurrence of dental decay and have their height and weight recorded. Dietary information obtained from a food frequency chart will be used to determine food and dietary patterns. Data analysis will use intention to treat and per protocol analysis and will use tests of independent proportions and means. Multivariate statistical tests will also be used to take account of socio-economic and demographic factors in addition to parental knowledge, behaviour, self-efficacy, and parent/child stress.

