## Methods

The study is a randomized controlled trial to test an oral health promotion intervention aimed at new-born children and their parents/carers in metropolitan Perth (population 1.7 million) and the regional cities of Bunbury (population 32,000) and Busselton (population 31,000) in Western Australia. It is a collaboration between Child and Adolescent Community Health and Dental Health Services (DHS), both Department of Health state-wide agencies delivering services for children.

Study participants will be recruited from all child/community health clinics in metropolitan Perth (fluoridated; 0.8 mg/L fluoride) and Bunbury/Busselton (non-fluoridated; < 0.2 mg/L fluoride). Children/parent dyads attending the child health clinics from these locations will be invited to participate, and the randomisation procedure will be based on individual randomisation stratified on the basis of residential location of Perth or Bunbury/Busselton. All new-born WA children are referred to their local child health clinic and receive a home visit from the child health nurse within 6 weeks of birth and are seen at the local child health clinics at regular intervals for health assessments throughout the early years. Parents of a new-born child presenting to selected child health clinics will be invited to participate and provided with information about the study including an oral health promotional package, a consent form and a self-complete questionnaire by the child health nurse. Upon receipt of consent to participate, consenting parent/caregiver and child dyads will be randomly allocated to either an intervention or control group by a central study coordinator using a computer generated random permuted blocks (block sizes; 4, 6, 8, 10, 12). The blocks will ensure that at most, an imbalance between test and control groups will be 6 participants at the conclusion of participant recruitment. Blinding of parent participants and counsellors will not be possible.

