The self-completed questionnaire will collect socio-demographic (age, sex, education level, family income, Aboriginality) and psychosocial information (oral health-related self-efficacy, knowledge about appropriate baby bottle use and children’s oral hygiene and belief in oral fatalism, instrumental social support and parental stress) and parental perceptions of treatment need and oral health care behaviours. The psychosocial measures have been used in other studies and have had their psychometric properties validated [38,39].

The psychosocial measures are shown in List of Psychocosial Measures. Oral health self-efficacy comprised nine items scored on a Likert scale from 1 (not at all confident) to 4 (very confident); higher scores indicate greater self-efficacy. Oral health knowledge on appropriate use of baby bottle and children’s oral hygiene comprise 10 items scored on a Likert scale from 1 (strongly agree) to 5 (strongly disagree); higher scores indicate better knowledge. Oral health fatalism comprised one item, “Most children eventually develop dental cavities”, scored 1 (strongly agree) to 5 (strongly disagree). The parenting stress instrument comprised six items scored on a Likert scale, 1 (never) to 5 (almost always); higher scores indicate higher levels of stress. The social support instrument comprised four items scored “yes” or “no”. Mean scores from sum of the item scores will be used for the oral health self-efficacy, oral health knowledge and parenting stress scales while the oral health fatalism score will be converted to a binary variable reflecting parent/caregiver agreement with the statement and each item of the instrumental social support instrument will be  presented as frequency scores and used as a binary variable.List of Psychological measures 

Oral Health Self-efficacy; scale, 1 = not at all confident, 4 = very confident

How confident do you feel that you are able to make sure that your child’s teeth are brushed before bedtime when you are:

1. Under a lot of stress?

2. Depressed?

3. Anxious?

4. Feeling like you do not have time?

5. Tired?

6. Worrying about other things in your life?

7. Bothered by your child crying?

8. Bothered because your child doesn’t stay still when you want him or her to brush?

9. Told by your child that he/she does not feel like brushing right now?

Knowledge of bottle use; scale, 1 = strongly agree, 5 = strongly disagree

1. Putting a baby to bed with a bottle helps the child to be better fed.

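### The location stratum is named in no group comparison, and psychosocial outcomes are defined as changes with no stated baseline adjustment; naming both as covariates is a free improvement

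*Protocol article*

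**What the plan says.** The Methods section of the protocol article describes "individual randomisation stratified on the basis of residential location of Perth or Bunbury/Busselton". It gives the areas' water supplies as "metropolitan Perth (fluoridated; 0.8 mg/L fluoride) and Bunbury/Busselton (non-fluoridated; < 0.2 mg/L fluoride" and their sizes as "metropolitan Perth (population 1.7 million) and the regional cities of Bunbury (population 32,000) and Busselton (population 31,000".

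In the Data analysis section, the comparison of decay and obesity with group allocation is introduced by "Univariate analyses will also be used to examine the association between the primary outcomes". The Methods paragraph of the abstract agrees, announcing two-sample tests of proportions and means. The next paragraph of Data analysis adds: "Multivariate analysis will be used to control for potential confounding factors to examine the effects of treatment strategies", by linear, logistic or Poisson regression. It does not list the confounders. The abstract says only that the multivariate tests will "take account of socio-economic and demographic factors in addition to parental knowledge, behaviour, self-efficacy, and parent/child stress".

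On the psychosocial outcomes, the Measures section states: "Secondary outcome measures will be changes in knowledge, attitude, behaviour and self-efficacy of parents". Aim 1, at the end of the Background, likewise compares the arms on change at 12 and 36 months, and adds parental stress. Baseline values of these measures are collected.

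**The concern.** A factor used to stratify randomisation belongs in the analysis. Stratified allocation balances the arms on it, so a test that omits it leaves between-stratum variation in the error term and gives a standard error larger than the design earned. Here one area is fluoridated and the other is not, so location is plausibly prognostic for decay.

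For the psychosocial scales, a plain comparison of changes subtracts the whole baseline score, noise included, and carries a chance baseline imbalance into the result. Adjusting for baseline by regression avoids both. All nine self-efficacy items concern brushing the child's teeth, while families enter when the infant is 6-12 weeks old. A low correlation between baseline and follow-up is therefore conceivable, and that is where change scores do worst. At stake is precision: a little for decay, possibly more for the secondary scales.

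**Working it through.** **1. The plan's own figure.** Inputs from Sample size and power: mean dmft 1.26 against 0.80, SD 2.63, 80% power, α = 0.05 (two-sided reproduces the stated figure; the article does not give the sidedness).

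n per arm = 2(1.960 + 0.842)² × 2.63² / 0.46² ≈ 513.1, rounded up to **514**. The stated figure reproduces, and it is for an unadjusted comparison.

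**2. Gain from the stratum.** With regional share p and regional difference D in mean dmft, the stratum explains R² = p(1−p)D²/SD² of the variance in a linear model, and required n falls by the factor 1−R². The article gives neither the recruited share nor D. The population share is 63,000/1,763,000 = 3.6%. Both inputs are assumptions; D = 1.26 means a regional mean 1.26 teeth higher.

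| p | D | R² | n per arm | Power at 514 |
|---|---|---|---|---|
| none (unadjusted) | – | 0 | 514 | 80.1% |
| 3.6% | 1.26 | 0.8% | 510 | 80.4% |
| 20% | 1.26 | 3.7% | 495 | 81.5% |
| 30% | 0.63 | 1.2% | 508 | 80.5% |
| 50% | 1.26 | 5.7% | 485 | 82.3% |

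For example, at p = 0.20: 0.16 × 1.5876 / 6.9169 = 0.037. Over shares of 3.6-50% and D of 0.3-1.26, the gain is 0.0 to 2.3 points of power.

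**3. Validity of the unadjusted test.** In 4,000 simulated trials per setting (1,028 children, normal outcome, exact balance within strata), its type I error was 4.6-5.0% at D = 1.26. It fell to 2.6% only in an extreme case (p = 50%, D = 2.5). Any departure is conservative.

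**4. Change score against baseline adjustment.** With equal SD s at both times and correlation r:

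- change score: 2(1−r)s²
- follow-up score alone: s²
- analysis of covariance: (1−r²)s²
- covariance / change: (1−r²)/[2(1−r)] = (1+r)/2

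| r (assumed) | Change | Covariance | Ratio | Less variance | Power if change score has 80% at 514 |
|---|---|---|---|---|---|
| 0.3 | 1.40 | 0.91 | 0.65 | 35% | 93.5% |
| 0.5 | 1.00 | 0.75 | 0.75 | 25% | 89.9% |
| 0.7 | 0.60 | 0.51 | 0.85 | 15% | 86.0% |

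Below r = 0.5 the change score is noisier than the follow-up score alone, since 2(1−r) > 1.

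**5. When the loss occurs.** If follow-up = a + b·arm + c·baseline, then change = a + b·arm + (c−1)·baseline. The arm effect b and its standard error are identical. Defining the outcome as a change therefore costs nothing if baseline is in the model, and costs the amounts above if it is not.

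**The case against.** The strongest reply is that the analysis paragraph is open, not closed. Adjusted regression is already planned for continuous, binary and count outcomes, and a condensed article commonly leaves covariate lists to a fuller document. The abstract's covariate classes do not name location, but they do not exclude it. The sections on psychosocial outcomes describe what is compared, not the estimator: the t-tests in Data analysis are attached to baseline factors by arm, and linear regression is the stated adjusted method for continuous outcomes. Parental knowledge, behaviour, self-efficacy and stress are themselves among the factors to be taken into account.

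Much of this stands. A reader might infer that the plan ignores the stratum, or that it commits to a plain change-score test and so forfeits up to a third of its information. The documents support neither. A reader might also take fluoridation as the stated reason for stratifying; the article reports the fluoride levels but gives no reason.

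Two things remain. The primary comparison is stated, not left open, and it is univariate, so it cannot contain the stratum. And the psychosocial covariates in the abstract carry no time point, while the Background and Data analysis sections treat the same measures as mediators. Naming them there does not establish that each outcome's baseline value is in its own model.

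**Conclusion.** The point holds as a no-cost improvement. The stated univariate comparisons of the primary outcomes omit the randomisation stratum, no analysis names it, and no baseline adjustment is stated for outcomes defined as changes.

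For decay, the size is small: about 1-4% of dmft variance for an assumed regional share of 3.6-20% with D = 1.26, and at most 2.3 points of power over the wider ranges tried. It would be wrong to infer that the unadjusted test is invalid, since its error, if any, is conservative. These figures are for dmft as a continuous outcome. For obesity the documents give no reason to expect location to be prognostic, so the case there is consistency with the design.

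The larger figure, 15-35% less variance, rests on assumed correlations of 0.7-0.3 and equal SDs, and on baseline being omitted. It concerns secondary outcomes only; decay has no baseline value at 6-12 weeks of age. A low correlation for the self-efficacy items is conjecture, and still more so if extended to knowledge and stress.

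**What to change.** In Data analysis, state that:

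- the reported intention-to-treat comparison for decay and for obesity is a regression on arm and location stratum, using the model families already listed;
- the knowledge, self-efficacy and parental stress scale scores at 12 and 36 months are each regressed on arm, the baseline score of the same scale, and stratum;
- the unadjusted tests are kept as supportive.

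Adding education and family income, which the baseline questionnaire already collects ("The self-completed questionnaire will collect socio-demographic (age, sex, education level, family income, Aboriginality"), is optional and not part of this point.

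The cost is wording only. Location is known at randomisation, and the baseline scales are already in the questionnaire. No change to sample size, visits or data collection is needed.

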## Background

There is little information available on the prevalence of early childhood dental decay in Australia. The most recent report on Australian children’s dental health indicated that, among 4-year-olds in 2005, approximately 37 percent of children had at least one decayed baby tooth. On average, there were 1.84 decayed, missing or filled baby teeth (dmft), of which 84 percent comprised of untreated dental decay [1]. In another study, parental report of dental decay experience (cavities, fillings or extractions) among preschool children (aged 2–3 years) was approximately 3% nationally with substantial variation between the States and Territories [2].

Information available from the Western Australian Dental Health Service (DHS) suggests that the majority of children that register with the Service at age five had not attended any dental care facility and were unlikely to have received any specific oral health care information. The mean decay experience (dmft) of WA 5-year-olds in 2009 was 1.26 of which 1.03 (82%) was the “d” component (untreated dental decay) (personal communication: DHS, 2009). One in three 5-year-old children examined in WA was affected by dental decay and one in ten had more than five teeth affected with dental decay, the majority of which was untreated. Severe untreated decay affects a child’s growth, body weight, quality of life as well as cognitive development, and the effects extend beyond the child, to the family, the community and the health care system [3-5].

Data from elsewhere suggest that the decay experience among children is increasing in Australia. A report from South Australia (SA) showed that, for children attending the School Dental Service in SA, the decay experience among 6–7-year-olds in 1998 was 1.16 and nearly doubling to 2.29 in 2008; and among 5-year-olds the decay experience in 2008 was 1.89 of which 1.2 was untreated decay, and 44% of the children were affected with decay [6].

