### Sample size and power

Sample size of approximately 514 children in each arm of the trial is required to detect a 35% reduction in dental decay experience [based on decay experience of children within DHS; dmft 1.26 (SD 2.63), test dmft 0.8] with a probability of 0.8 (power 80%) and rejecting the likelihood of no difference at probability 0.05 (α = 0.05) [49]. This is a conservative sample allowance to detect a difference, since an Australian intervention study on early childhood decay found 79% reduction in decay incidence among 20 month-old children [23]. Allowing for drop-off and loss to follow-up over the following 3 years, an initial sample of approximately 750 in each group of the trial would be required (an earlier study of caries prevention within SDS found attrition rate of 9% per annum over two years [50]). The estimated sample size will have a power of 94% to detect a 35% reduction in the prevalence of early childhood decay (dmft > 0; from 0.25 to 0.16) between the groups (α = 0.05). The estimated sample size will also permit detecting a 33% difference in prevalence of overweight or obese children between the two groups (from 20% to 14%) with 80% power and α = 0.05.

Ethical approval for the study has been provided by the University of Western Australia Human Research Ethics Committee (RA/4/1/4469), the Princess Margaret Hospital for Children Ethics Committee (Reg. No. 1900/EP), and the WA Country Health Services Ethics Committee (ref 2011:05). Figure 1 shows the study sample and pathway for the study participants in the test and control arms. All child participants will have the same clinical and other information collected again at approximately 5 years of age. Sample maintenance strategies, including card mail-outs on the child’s birthday, change of address notification and regular updating of the study will be undertaken.

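### Poisson regression for child-level decay counts, with no allowance for overdispersion, does not fit the plan's own dmft figures and inflates the type I error

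*Protocol article*

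**What the plan says.** In the protocol article, Data analysis defines the outcome as a count: "Oral health outcomes will be defined by counts of decayed, missing and filled teeth/surfaces". For the multivariate analysis it lists linear regression for continuous outcomes, logistic regression for binary outcomes, and "Poisson regression to estimate rates of disease occurrence". The next sentence deals with correlation, but only below the level of the child: "Site-specific measures of caries incidence within an individual will use GEE analysis to control for correlation within an individual". The effect measures follow: "Effect size will be estimated through calculation of incidence density ratios for dental decay and prevalence ratios for obesity". The significance level is 0.05. No dispersion parameter, robust variance or negative binomial alternative is named for the child-level counts.

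Sample size and power plans on "dmft 1.26 (SD 2.63), test dmft 0.8". Background gives the source of the control mean: "The mean decay experience (dmft) of WA 5-year-olds in 2009 was 1.26". The same paragraph describes the distribution: "One in three 5-year-old children examined in WA was affected by dental decay", and one child in ten had more than five affected teeth.

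Measures makes decay incidence a primary outcome, with examinations at 24 and 36 months. Decay at 5 years is a long-term outcome.

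**The concern.** Poisson regression with its usual model-based standard errors assumes that the variance of the count equals its mean. Decay counts in young children pile up at zero and have a long right tail, and the protocol's own figures show this. If the variance is several times the mean, the rate ratio is still estimated sensibly, but its standard error is too small, its confidence interval too narrow and its p-value too low. A chance difference between arms would then be declared a significant effect on decay far more often than the stated 5%. More participants do not cure this, because the standard error is wrong by the same factor at any sample size.

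Decay incidence is a primary outcome, and the Discussion expects the findings to be taken into policy and practice.

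**Working it through.** **Inputs.** Control mean dmft 1.26, SD 2.63, intervention mean 0.8, 514 evaluable children per arm, 80% power, α = 0.05, and 25% control prevalence (Sample size and power). One in three children affected and one in ten with more than five affected teeth, at age 5 (Background). Sidedness is not stated; two-sided reproduces the plan's number.

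**1. The plan's own figure.** Two-means formula: n = 2 × SD² × (1.96 + 0.842)² / difference². With SD² = 6.917 and difference = 1.26 − 0.8 = 0.46, n = 2 × 6.917 × 7.849 / 0.2116, which gives 514 per arm after rounding up. The stated figure is reproduced, so the trial was sized on the full, overdispersed variance.

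**2. The variance that the named model assumes.** Under a Poisson model the two variances would be 1.26 and 0.8. The same formula would give (1.26 + 0.8) × 7.849 / 0.2116, about 76 per arm. In the control group the sample size uses a variance of 6.92 where the named model uses 1.26.

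**3. Dispersion.** φ = 2.63² / 1.26 = 6.917 / 1.26 = 5.49, and √φ = 2.34. Model-based standard errors are too small by a factor of 2.34.

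**4. Check against the described distribution.** A Poisson count with mean 1.26 has P(0) = e^(−1.26) = 0.284, so about 72% of children would be affected and about 0.2% would have more than five affected teeth. Background reports about 33% and 10%. A negative binomial matched to the mean and SD has k = 1.26² / (6.917 − 1.26) = 0.281 and P(0) = 0.62, so 38% affected, much nearer to the reported third.

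**5. Type I error on the planning figures.** Actual size of a nominal 5% two-sided Wald test = 2 × P(Z > 1.96 / √φ) = 2 × P(Z > 1.96 / 2.34) = 40.3%. Coverage of the nominal 95% interval is then about 60%. Simulation of 20,000 null trials with 514 per arm:

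| Counts (mean 1.26, SD 2.63) | Model-based Poisson | Robust SE | Pearson-scaled |
|---|---|---|---|
| Negative binomial | 40.2% | 5.2% | 5.1% |
| One-third affected, hurdle | 40.8% | 5.3% | 5.2% |

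The result hardly depends on the shape of the distribution, and either correction restores the nominal level.

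**6. Younger ages.** The document gives no dmft mean or SD at 24 or 36 months. Assume that k = 0.281 holds, so that φ = 1 + mean / k. At the planned 25% prevalence, (k / (k + mean))^k = 0.75 gives a mean of about 0.50.

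| Mean dmft | φ | Type I error |
|---|---|---|
| 1.26 | 5.49 | 40% |
| 0.8 | 3.85 | 32% |
| 0.6 | 3.14 | 27% |
| 0.5 (25% affected) | 2.78 | 24% |
| 0.3 | 2.07 | 17% |
| 0.1 | 1.36 | 9% |

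Simulation at means 0.6 and 0.3 gave 26.7% and 17.0%. The error falls with the mean but stays above 5% throughout.

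**The case against.** Several objections have force.

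- **The article is condensed and the SAP is not shown.** The text does not rule out robust or scaled standard errors, and it promises suitable parametric and nonparametric methods in general terms. An SAP that added either correction would restore about 5%. This stands as a limit on certainty. It does not remove the point, because the protocol names a method, qualifies it for correlation at site level only, and gives planning figures that contradict that method's variance assumption.
- **The 40% belongs to 5-year-olds.** A reader might infer that the primary analysis at 24 and 36 months has a 40% false-positive rate. The documents do not support that. Background also cites about 3% parent-reported decay at ages 2 to 3, where the same k would give only about 6%. That report covers cavities, fillings or extractions, whereas the trial's outcome also counts non-cavitated lesions, so it is not a direct guide either.
- **The incidence density ratio is not tied to a model.** A reader might take it to be, for certain, the adjusted Poisson estimate. That is the natural reading, but the text does not say so, and the sentence follows the one on site-level GEE. A ratio taken from that GEE would not have this fault.
- **Other decay analyses are planned.** The univariate comparisons, the logistic model for prevalence and the site-level GEE are unaffected, so not every test of decay is compromised.

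A reader might also infer a clash between logistic regression and prevalence ratios for obesity. Data analysis does not say that the ratio comes from the logistic coefficient, and a prevalence ratio can be obtained in other ways, so that inference is not supported.

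**Conclusion.** The point holds: the method is wrong as written for child-level decay counts. The size of the error must be stated with its condition. It is about 40% on the dmft figures that the protocol adopts for planning, and roughly 9% to 24% for means between 0.1 and 0.5, which may be nearer to the ages of the first examinations. That range rests on carrying k = 0.28 over from the 5-year-old figures; the true dispersion at 24 and 36 months could be larger or smaller. All these figures assume model-based standard errors, which is what an unqualified Poisson regression means. The point is confined to the multivariate Poisson analysis of decay and to incidence density ratios derived from it.

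**What to change.** In Data analysis, replace the unqualified Poisson model. State that all child-level dmft and dmfs counts, and the incidence density ratios based on them, will be analysed by negative binomial regression or by Poisson regression with robust (sandwich) standard errors. Choose one of the two before outcome data are seen. Say also which model yields the reported incidence density ratio. If an SAP already specifies such a correction, the protocol wording should be aligned with it.

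The change is one or two sentences and needs no further data or participants. Confidence intervals will be wider than under the uncorrected model, which is the correct width. The stated sample size needs no change on this account, because it already uses the full SD of 2.63.
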